### Limitations

Due to its pragmatic nature, this study is primarily a test of effectiveness, but the attention-placebo control group has the characteristics of an efficacy trial. One of the challenges in hiring and training personnel was to simultaneously prepare them for a randomized controlled trial and a real-world SBI. As a result, there are limitations to transportability. Most notably, the training period for HEs was a full month, probably longer than can realistically be expected for service programs. However, a large portion of the training was dedicated to research concepts, which accounts for most of the disparity between the training duration of this study and what practitioners could reasonably accommodate. The other issues of transportability are related to funding and the ongoing question of whether SBI services should be delivered by paraprofessionals or trained medical staff. Enthusiasm for SBI services has been building in California in recent years, and the CASBIRT health educator model, upon which this study was built, has been recognized as a realistic alternative in health-care settings where medical personnel are unavailable [34]. Similarly, Bernstein and colleagues [5] found that, regardless of setting, SBI programs tend to migrate to the use of HEs over medical professionals. They also found that, although SBI funding is not guaranteed, as the model continues to result in cost savings, and as new billing codes are activated, it becomes increasingly likely that there will be funds to support these positions.

Although the HEs in this study were successful in their recruitment efforts, and despite concerted cohort maintenance efforts, a considerable number of participants were lost to follow-up, a common problem in studies of drug users [35,36]. Project staff aggressively followed up with participants by phone and mail and made home visits when it was feasible and safe. Study design did not allow for follow-up with participants who were incarcerated or enrolled in inpatient treatment; if it had, it is possible that the follow-up rate would have been higher. A low follow-up rate is of concern because of potential threats to validity, especially to the degree that the characteristics of those lost to follow-up differ by experimental condition. We plan to conduct a thorough analysis to test attrition bias and to conduct outcome analyses that adjust for missing data.

Although it was an advantage to collect hair at the follow-up assessment, hair was not collected at baseline. It is possible that non-drug users could have been enrolled in the study, although reporting of drug use that did not occur is thought to be minimal [37]. We were not able to test for all possible drugs, although participants were tested for the most common drugs of abuse in San Diego County. Like any biological measure, hair samples have shortcomings, and statistical and technical problems related to their use to validate self-reports of drug use have been reported [38]. Adequacy of screening instruments is also a concern; for example, although the DAST is widely used and its psychometric strengths are well-established as a diagnostic tool, there is a lack of information about its validity in an emergency-department setting with a wide range of patients. In addition, although trained in research methods and experimental design, the HEs could have contaminated the groups by providing a drug use intervention to participants in the control group.

Comparing our results to similar studies will be difficult given the lack of randomized controlled trials for drug SBI, differences in the types of drug users targeted, and other important methodological differences. Probably the most similar published study was a randomized trial of brief motivational intervention in clinics for out-of-treatment cocaine and heroin users screened by peer interventionists during an urgent medical visit [8], but that study involved higher risk drug users than those in our sample. We plan to compare our results to the Bernstein et al. study [8] to the degree possible, as well as other studies that may be published soon.

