#### Module 2: illicit drug use

This module included an overview of the biological mechanisms by which drugs of abuse act, their potential impacts on low risk users, as well as the diagnoses of abuse and dependence [19]. It also covered common drugs of abuse, their street names, routes of administration, short- and long-term effects, and consequences of ongoing use, including use at low risk levels or by individuals who do not meet diagnostic criteria for abuse or dependence. According to data from CASBIRT, the most common drugs of abuse in San Diego are marijuana, methamphetamine, and cocaine, so particular attention was paid to these substances. The HEs were taught about common treatment modalities, including detoxification and therapeutic communities (inpatient and outpatient). They were provided with lists of local resources to make appropriate referrals, as referral to treatment was routinely offered to experimental group participants who fell into higher categories.

The most nuanced elements of this module were the two areas that relied heavily on HE use of critical thinking skills to make well-reasoned situational judgments. The first such area was a harm reduction approach. Although abstinence is the best option with respect to illicit drug use, it is often unrealistic to expect that an individual will be willing and able to immediately achieve abstinence, even following a powerful brief intervention conducted at a teachable moment. For this reason, HEs could employ a harm reduction approach for participants who were not yet ready to consider abstinence [7]. By training the HEs about the positive outcomes associated with meaningful reductions in illicit drug use, they became prepared to negotiate interim reductions while still ultimately advocating for abstinence.

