### Participant recruitment and follow-up

Participant recruitment was conducted from April 2010 through June 2011, with a total of 700 subjects enrolled. Modifications to the experimental protocol were minimal. Figure 1 presents a CONSORT diagram of the flow of patients through the trial. Over 18,000 patients were approached and screened for their eligibility and interest in participating. The great majority of those excluded did not meet the eligibility criteria (e.g., their alcohol use risk exceeded their drug use risk). Of those who were eligible to participate, 29% were excluded, with 9.5% refusing and 19.5% excluded for other reasons (e.g., being interrupted for a medical procedure, becoming too sick or too sleepy to continue). The six-month follow-up rate was 43% with no difference in reasons for loss by condition.

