### Outcome measures and analyses

Mixed model analysis of variance (ANOVA) procedures within a general linear model framework will be conducted on the key self-reported outcomes measured by the ASI-Lite. The ASI-Lite composite scores of recent drug use and related medical problems, psychiatric problems, and alcohol use will be analyzed along with health-care utilization outcomes to assess differential change by condition. Because of potential bias introduced by a less-than-ideal response rate, two sets of analyses for the self-reported data will be conducted: complete-case analyses of 294 participants with longitudinal data and intention-to-treat analyses using multiple-imputation data to deal with loss to follow-up (N = 700). With multiple imputation, missing follow-up values are replaced by a series of plausible values rather than by a single value [27-30]. For each outcome, we will use multiple imputation with a chained equation approach to create five imputed data sets and pool these results. Imputed outcome values will be predicted from baseline drug and alcohol use variables, gender, age, income, and drug avoidance self-efficacy. In addition to changes in composite scores, the ASI-Lite drug use scores will be dichotomized into a past 30-day drug use abstinence variable (yes/no) measured at the six-month follow-up. Results of hair analysis will be used to verify abstinence reports. When hair analysis is positive for drug use and self-report is negative for drug use, the participant will be considered nonabstinent.

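### Both planned analyses treat a 58% loss as ignorable, although the design itself made incarcerated and inpatient-treatment participants missing

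*Protocol article*

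**What the plan says.** Outcome measures and analyses states that "two sets of analyses for the self-reported data will be conducted". One uses the 294 participants with longitudinal data. The other is an intention-to-treat analysis of all 700 by multiple imputation with chained equations and five imputed data sets. The predictors are listed: "Imputed outcome values will be predicted from baseline drug and alcohol use variables, gender, age, income, and drug avoidance self-efficacy". All are baseline quantities; reason for loss and status at six months are not among them.

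On the loss itself, Participant recruitment and follow-up reports: "The six-month follow-up rate was 43% with no difference in reasons for loss by condition". Limitations adds that "Study design did not allow for follow-up with participants who were incarcerated or enrolled in inpatient treatment", concedes that low follow-up threatens validity, and promises a test of attrition bias and outcome analyses that adjust for missing data.

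On treatment entry, Module 2 says that "referral to treatment was routinely offered to experimental group participants who fell into higher categories". The treatment modalities taught there include inpatient care.

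**The concern.** Complete-case analysis and imputation from baseline each take the missing to resemble the observed, the first given its model terms and the second given the listed baseline variables. Neither condition is credible by default here. Being in jail or in inpatient treatment at six months comes about after baseline and is plausibly tied to drug use in the interval, which is what the trial measures. Treatment entry may also be related to arm, because routine referral is described for experimental participants in the higher risk categories.

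More participants are missing than observed, so the assumption carries most of the N = 700 result. If the two analyses agree, a reader will take that as reassurance. They share the assumption that is in doubt, so agreement says little about it. Bias could go either way: successes after treatment entry may be missing, and so may continuing heavy users.

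**Working it through.** **Inputs.** From the article: 700 randomised, 346 and 354 by arm (Table 1); 294 with longitudinal data; follow-up stated as 43%. Assumed, because the article does not give them: equal loss in both arms, hence about 147 completers per arm, and an abstinence rate of 10%, 20% or 30%.

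**The plan's own figure.** 294/700 = 42.0%, so 700 − 294 = 406 are missing (58.0%). The stated 43% would be 0.43 × 700 = 301. The one-point gap does not matter here; I use 0.58.

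**Shift formula.** Let δ be the true mean among the missing in an arm minus the mean assigned to them (by imputation, or implicitly by the observed cases). With missing share m in each arm:

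true difference − estimated difference = m × (δ_E − δ_C) = 0.58 × (δ_E − δ_C)

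A differential of 5, 10 or 20 points gives 2.9, 5.8 or 11.6 points. If δ_E = δ_C, the shift is zero.

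**Yardstick.** Complete-case standard error of the abstinence difference: SE = √[p(1 − p) × 2/147]. The differential that moves the result by one SE is SE/0.58; by 1.96 SE, 1.96 × SE/0.58.

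| Assumed abstinence | SE (points) | Differential for 1 SE | Differential for 1.96 SE |
|---|---|---|---|
| 10% | 3.50 | 6.0 | 11.8 |
| 20% | 4.67 | 8.0 | 15.8 |
| 30% | 5.35 | 9.2 | 18.1 |

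These differentials are averages over all the missing, not over confined participants alone.

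**What confinement alone would have to do.** If only confined participants depart, and they differ from the other participants by an assumed 30 to 100 points, the differential equals the between-arm difference in the confined share of the missing times that gap. To reach 8 points, the share must differ by 8/1.00 = 8 to 8/0.30 ≈ 27 percentage points. To reach 16 points, it must differ by 16 to 53. A 5-point difference in share would shift the result by only 0.58 × 5 × 0.3 ≈ 0.9 to 0.58 × 5 × 1.0 = 2.9 points.

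No comparable figure can be worked out for the ASI-Lite composites, because the article gives no standard deviation for them.

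**The case against.** The strongest reply is that this is a condensed article. Sensitivity analyses commonly sit in the analysis plan, and the authors openly admit the threat and promise an attrition analysis. That is fair as far as it goes, and a fuller plan may already contain what is asked for. But the article does more than stay silent: it names the two analyses, lists the imputation predictors, and discloses a mechanism of loss that those predictors cannot represent. The attrition analysis need not stop at baseline variables, since reasons for loss were also compared. It still cannot examine outcomes that nobody observed.

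The second reply is that the article reports "no difference in reasons for loss by condition". This counts against a strong arm-differential route: if referral had moved many experimental participants into inpatient care, reasons for loss should differ. It weakens the concern without removing it. The text gives no counts by reason, and the same reason can go with different outcomes in the two arms.

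A reader might infer that only the experimental arm could be referred to treatment. The documents do not say so. Routine referral is described for that arm, and controls are said to receive no drug intervention, but referral of controls is nowhere ruled out.

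A reader might also infer that hair-verified abstinence has no analysis on all 700, because the two sets are stated for self-reported data. That is not supported either. Abstinence is a dichotomised ASI-Lite score that hair results can override, and the article says imputation is used for each outcome.

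**Conclusion.** The point holds in a limited form. Both named analyses rest on ignorable loss, 58% of participants are missing, and part of that loss was built into the design through post-baseline states plausibly linked to drug use. Agreement between the analyses would not show robustness.

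The documents do not show that bias exists, how large it is, or which way it runs. The number confined is not given, and the reported similarity of reasons for loss argues against a large difference between arms. The 6-to-9-point and 12-to-18-point thresholds rest on equal loss by arm and on assumed abstinence of 10% to 30%, with the complete-case standard error as yardstick. They show how far the result could be moved, not how far it has been. A sensitivity analysis should be added; nothing here invalidates the planned ones.

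**What to change.** Keep the two analyses in Outcome measures and analyses and add a third: a delta-adjusted (pattern-mixture) sensitivity analysis on the imputed N = 700 data, with delta varied separately by arm and the tipping point reported. Do this for the ASI-Lite drug composite and for 30-day abstinence.

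Where the recorded reasons for loss identify incarcerated or inpatient participants, report their numbers by arm and give them their own delta. State in advance that the conclusion will be qualified if it tips at a plausible delta.

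An analysis that counts every missing participant as nonabstinent need not be required. It would score inpatient entrants as failures when some may be treatment successes.

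The cost is a paragraph of plan text and extra runs on existing data; the abstract says outcome analysis was not yet complete. The separate delta depends on how finely reasons for loss were recorded, which the article does not say. The downside is a possibly more guarded conclusion.

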## Conclusions

The successful implementation of this study can be attributed largely to a customized training and development protocol, which led to a high level of skill mastery combined with a flexible approach. The HEs were thoroughly educated in the fundamental concepts, and then taught to think critically about participants’ motivations and perceptions about illicit drug use in order to achieve optimal results. This combination allowed the HEs to successfully recruit, screen, and intervene with large numbers of hospital patients in a way that would not have been possible with a traditional scripted approach. As a result of this innovative design, final results from this study will provide meaningful insight into the effectiveness of SBI for illicit drug use.
